### Enrolment

Patients evaluated at a multidisciplinary conference and afterward with a biopsy verified STS will be identified in Sundhedsplatformen (electronic patient records); the only information needed from the patient records prior to informed consent is when they will meet in the outpatient clinic. Patients eligible for inclusion will at their first outpatient visit to plan further final surgery be informed about the study written and orally. On the day of their surgery, written informed consent will be obtained if they want to participate in this study. No patient will have below 48 h to answer, complying with the Helsinki declaration [15].

All patients will be informed orally and written by the principal investigator, or colleague information will be given in a separate room allocated for only the patient and if wanted the assessor, so interruption does not occur. All patients will be asked if they want an assessor, and then a new meeting will be arranged, and the information will again be given by the principal investigator in a separate room allocated for the patient and the assessor.

The written informed consent gives the principal investigator, sponsor, and sponsor’s representatives as well as any control authority direct access to obtain information in the patient’s medical record, etc., including electronic medical record, in order to see information about the subject’s health, which is necessary for carrying out the research project and for control purposes, including self-monitoring and quality control, which they are required to perform.

The participants are covered by the Danish Patient Compensation Association (Fig. 1).

**Fig. 1 Fig1:**
[figure not shown]
CONSORT expected flow diagram

### Criteria of inclusion

Surgery for a deep-seated STS of an extremity or the trunk wall at Rigshospitalet

### Criteria of exclusion

Age < 18 yearsWound closure not possible without plastic surgery (pedicled or free flaps)Low malignant (Trojani grade 1) [16] STS or borderline tumorsPre- or postoperative chemotherapyPreoperative radiotherapy to the local siteAllergic or hypersensitive to acrylic adhesives or silverUnwilling or unable to provide informed consentInability to comply with planned study proceduresPatients with metastatic diseasePatients with ischemic surgery such as bypass or endovascular prosthesis

### Drop out criteria

Did not want to participate

### Variables collected

AgeGenderLifestyle factors such as alcohol consumption, caffeine intake, smoking habits, BMI, and exerciseComorbidities, including medical treatments (including but not limited to hypertension, hypercholesterolemia diabetes mellitus/HbA1C, dialysis dependence, chronic venous insufficiency, end-stage renal disease, congestive heart failure)Radiation regimeOperation timeBlood loss at surgeryPathologyTumor location, size, grade depthPostoperative medical treatmentImages

### Randomization

All 160 patients will in the operating room be randomized (randomization with 80 patients in each group) to receive one of the two treatments:

Group A: Standard wound closure with staples and conventional wound dressing

Group B: Standard wound closure with staples and NPWT (PREVENA PLUS™ Incision Management System)

Block randomization with 8 patients in each block stratified for upper extremity/truncal wall or lower extremity STS will be performed using a verified computerized irreversible application—the Research Electronic Data Capture (REDCap). The randomization sequence will be computer-generated. This study is not blinded.

The study takes place at the Department of Orthopedic Surgery, Rigshospitalet, University of Copenhagen. Patients will be followed in our outpatient clinic; the surgeries will be performed by specialized orthopedic tumor surgeons. Rigshospitalet is a tertiary multidisciplinary sarcoma center performing highly specialized tumor surgeries.

### Follow-up

The patient’s wounds will be followed by a member of the department staff or research group with photo documentation on day 0, day 7, at definitive wound healing (removal of staples), 4 months postoperatively, and in case of major wound complication.

Follow-up from day 7 and further on will be performed in the outpatient regime, at Rigshospitalet, orthopedic department; patients will be convened through e-books (secure platform for digital postboxes), and, if necessary, transport will be provided.

Preoperative, after 4 months, and 1 year quality of life will be evaluated with European Quality of Life - 5 Dimensions (EQ-5D) [17]; furthermore, Musculoskeletal Tumor Society Score (MSTS) [18] and Toronto Extremity Salvage Score (TESS) [19] will be used to evaluate function 4 months and 1 year postoperatively depending on surgery location (Fig. 2).

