### Secondary study endpoints

Length of hospital stay, readmission to hospital for treatment of a wound complication, time to primary wound healing and removal of staples (ready for radiation therapy), deep infection, postoperative seroma development, MSTS [18], and TESS [19] 4 months and 1 year postoperatively; furthermore, quality of life will be evaluated with EQ-5D [17] preoperatively, at 4 months and 1 year.

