### Statistical analysis

Fisher’s exact test will be used for categorical variables.

Depending on if the data could be considered normally distributed or not, a *t*-test for unpaired data or Mann–Whitney *U* test will be used for continuous variables.

Kaplan-Meier survival analysis will be used for overall survival (with log-rank test for comparison of groups). In case of an assumption of a difference in time to delayed wound healing, competing risk analysis will be used to address differences between the groups with death and amputation as competing factors.

All analyses will be performed in accordance with the intention-to-treat principles.

Two-sided *p*-values below 0.05 will be considered statistically significant.

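### MSTS and TESS fall under an unadjusted two-sample test that ignores the randomisation stratum and baseline data already collected, giving up some precision on these secondary endpoints

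*Protocol article*

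**What the plan says.** The protocol article's Follow-up section says that MSTS and TESS "will be used to evaluate function 4 months and 1 year postoperatively depending on surgery location". Its Secondary study endpoints section agrees: "MSTS [18], and TESS [19] 4 months and 1 year postoperatively". Neither section gives a preoperative assessment of function. EQ-5D is treated differently: "quality of life will be evaluated with EQ-5D [17] preoperatively, at 4 months and 1 year".

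The Statistical analysis section sets one rule for all continuous variables. "Depending on if the data could be considered normally distributed or not", the comparison uses the t-test or its rank alternative (the "test for unpaired data or Mann–Whitney *U* test will be used for continuous variables"). No covariate or stratum is named.

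The Randomization section states that allocation is "stratified for upper extremity/truncal wall or lower extremity STS", in blocks of 8. The Variables collected section lists tumour location and size.

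**The concern.** The trial stratifies its randomisation by tumour site, and Follow-up links the use of the function scores to the location of surgery. Site is therefore a factor that the plan itself treats as relevant, yet the only stated analysis ignores it. Two other plausible predictors of postoperative function, preoperative EQ-5D and tumour size, will also be on file and are not used.

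Two things follow if these variables predict function. First, variation unrelated to the dressing stays in the comparison and widens the interval. Second, stratified blocks already remove most of the between-site component from the true sampling variance of the treatment difference, but an unadjusted t-test still counts it. The reported standard error is then too large and the test conservative.

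Four comparisons are affected: two scores at two times. Because the choice between the two tests depends on the data, the plan also does not guarantee a mean difference with a confidence interval for these endpoints.

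**Working it through.** **The plan's own figure.** The only calculated figure is the sample size for the primary endpoint. With 17% against 3.4% (an 80% reduction), two-sided 5%, 80% power and no continuity correction:

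n = [1.96·√(2·0.102·0.898) + 0.8416·√(0.17·0.83 + 0.034·0.966)]² / 0.136² = 76.6, rounded up to 77 per group, or 154.

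This matches the stated 154. The present point does not touch it.

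**Inputs for the function scores.**
- From the document: 77 per group (Calculation of sample size), "randomization with 80 patients in each group" as planned recruitment, and two-sided 5%.
- Assumed, because the document gives no value: a true difference of 0.4 SD, and a multiple correlation R between the covariates and the score.

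**Power with and without adjustment, 77 per group.** SE = √(2(1−R²)/77) in SD units; power = Φ(0.4/SE − 1.96).

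| R | Variance removed | SE | Power |
|---|---|---|---|
| 0 (unadjusted) | 0% | 0.161 | 69.9% |
| 0.2 | 4% | 0.158 | 71.7% |
| 0.3 | 9% | 0.154 | 73.9% |
| 0.4 | 16% | 0.148 | 77.3% |
| 0.5 | 25% | 0.140 | 81.8% |

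**The same at 80 per group.** The unadjusted test has 80% power for √(2/80)·(1.96 + 0.8416) = 0.443 SD. At that difference, adjustment gives 81.6%, 83.6%, 86.4% and 89.9% for R = 0.2, 0.3, 0.4 and 0.5. In equivalent patients, 160/(1−R²) runs from 167 at R = 0.2 to 213 at R = 0.5.

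**What the stratum alone could do.** Assume a 1-SD difference in function between strata and a share f of patients in one stratum. The stratum's share of total variance is f(1−f)/(1 + f(1−f)). For f = 0.3 this is 0.21/1.21 = 17.4%; for f = 0.4 it is 0.24/1.24 = 19.4%. The unadjusted standard error would then be too large by a factor of 1/√(1−0.174) = 1.10 or 1/√(1−0.194) = 1.11. Both the gap and the shares are assumptions.

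**A limit of the table.** It treats the covariates as not balanced by design. For the stratum, the estimator's true variance is already reduced, so the unadjusted test does slightly better than the first row. If all of R = 0.4 came from the stratum, unadjusted power would be Φ((0.4 − 1.96·0.1612)/0.1477) = Φ(0.57), about 71.5%. The gain would then be from 71.5% to 77.3%, not from 69.9%.

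**Cost if the covariates are useless.** Three covariates multiply the variance by about (154−3)/(154−6) = 1.020 at 77 per group, and 1.019 at 80. Adjustment breaks even at R² = 1 − 148/151 = 0.020, that is R of about 0.14. Net of this cost, the variance ratio at R = 0.2 is 0.979, a gain of about 2%.

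**The case against.** The best defence is that the Statistical analysis section is short, assigns default tests by type of variable, and names neither MSTS nor TESS. Covariate models for secondary endpoints often sit in a statistical analysis plan, and that is not shown. This lowers the weight of the point but does not remove it: the document states an unadjusted test for continuous variables, so an adjusted model would replace stated text and not fill a gap.

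The objection to the size stands. Every quantity behind the gain is assumed, and at R = 0.2 the gain is under 2 percentage points of power. The 77 per group belongs to the 4-month primary endpoint. Fewer patients may contribute at 1 year, or to a score whose use depends on location.

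A reader might infer more than the text supports:
- That scores are pooled across locations or instruments. Nothing says so; the text says only that their use depends on location.
- That the comparison is biased. It is not: randomisation protects the unadjusted test, and stratified blocks limit imbalance in site. Chance imbalance matters only for EQ-5D and tumour size, which are not stratified.
- That the lack of a preoperative MSTS or TESS must be repaired. Recruitment has started, so a baseline added now would be missing for everyone already enrolled, and the adjustment does not need it.

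A linear model also needs an answer for clearly non-normal scores, which the plan's rank test was meant to give.

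**Conclusion.** The point holds as one of efficiency. The stated analysis of MSTS and TESS is valid but leaves out a stratification factor and two baseline variables that the trial plans to collect. The loss cannot be computed from the document. Under the assumed 0.4 SD difference with 77 per group, it is about 2 percentage points of power at R = 0.2 and about 12 at R = 0.5, and somewhat less to the extent that the correlation comes from the stratum. The primary endpoint and its sample size are unaffected. The change is worth making because the worst case costs about 2% in variance and no further data are needed.

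**What to change.** Before outcome data are analysed, amend the Statistical analysis section so that MSTS and TESS, at 4 months and at 1 year, are each compared with a linear model containing arm, randomisation stratum, preoperative EQ-5D and tumour size. Report the adjusted mean difference with its 95% confidence interval.

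If scores are clearly non-normal, add robust standard errors or a stratified rank test as a sensitivity analysis. State a simple rule for a missing preoperative EQ-5D, for example mean imputation of the covariate, so that no patient is dropped for it. Tumour size can serve even if it is taken from the specimen, since the dressing cannot affect it.

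The cost is analysis wording only, with no new assessments and no added patients.

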**Fig. 2 Fig2:**
[figure not shown]
SPIRIT figure. Schedule of enrolment, allocation, interventions, and assessments of the 160 STS patients

### Patient involvement

There has not been any public or patient involvement when designing this protocol.

### Main hypotheses

The use of NPWT will result in a decrease of postoperative wound complications after surgical removal of deep-seated high-malignant STS of the extremities or trunk wall compared to a conventional wound dressing.

### Primary study endpoints

A major wound complication defined as in O’Sullivan et al. [11]:A secondary surgery under anesthesia for wound repairs such as debridement, operative drainage, and secondary wound closureWound management without secondary surgery; this includes invasive procedure without anesthesia such as aspiration of seroma and readmission for wound care such as intravenous antibiotic or persistent deep packing within 4 months (120 days) after surgery

### Secondary study endpoints

Length of hospital stay, readmission to hospital for treatment of a wound complication, time to primary wound healing and removal of staples (ready for radiation therapy), deep infection, postoperative seroma development, MSTS [18], and TESS [19] 4 months and 1 year postoperatively; furthermore, quality of life will be evaluated with EQ-5D [17] preoperatively, at 4 months and 1 year.

### Statistical analysis

Fisher’s exact test will be used for categorical variables.

Depending on if the data could be considered normally distributed or not, a *t*-test for unpaired data or Mann–Whitney *U* test will be used for continuous variables.

Kaplan-Meier survival analysis will be used for overall survival (with log-rank test for comparison of groups). In case of an assumption of a difference in time to delayed wound healing, competing risk analysis will be used to address differences between the groups with death and amputation as competing factors.

All analyses will be performed in accordance with the intention-to-treat principles.

Two-sided *p*-values below 0.05 will be considered statistically significant.

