## Methods/design

### Study design

The study design is as follows: non-blinded single-center randomized (1:1) controlled trial, with parallel groups and block randomization of 8 patients in each group comparing NPWT versus conventional wound dressing and postoperative wound complications after surgical removal of deep-seated high-malignant STS of the extremities or trunk wall.

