### Calculation of sample size

In the study of O’Sullivan et al. [11], a major wound complication within 4 months postoperatively was identified in 16 out of 94 (17%) STS patients treated with surgery and postoperative radiation therapy. There exist no studies evaluating the effect of NPWT on wound complications after surgery for STS combined with postoperative radiation therapy. However, in retrospective studies, it was found that NPWT reduced the risk of wound complications from 47 to 8% (83% reduction) in patients with lower extremity STS treated with preoperative radiation [14] and from 27 to 7% (75% reduction) in patients undergoing hip and knee revision surgery [20].

In a study design with an 80% risk of avoiding type II error, a 5% risk of type I error, and an 80% wound complication risk reduction in a population similar to the study by O’Sullivan et al. [11], we will need to include 154 STS patients (77 in each group) in an RCT.

To make allowance for dropouts (since the follow-up period regarding the primary study endpoint is only 4 months = 120 days few dropouts are expected) during the study period, we plan to include 160 patients.

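### The 80% power attached to 154 patients does not hold under Fisher's exact test: it is 76.5% at 154 and 78.7% at 160 (minor)

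*Protocol article*

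**What the plan says.** The primary endpoint (Primary study endpoints) is a major wound complication: either repeat surgery for the wound or specified non-surgical wound management, ending with "persistent deep packing within 4 months (120 days) after surgery". Each patient either has one or does not, so the outcome is binary.

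For such outcomes the Statistical analysis section gives one rule: "Fisher’s exact test will be used for categorical variables". The same section adds "Two-sided *p*-values below 0.05 will be considered statistically significant". Competing-risk methods are mentioned only for time to delayed wound healing, and the log-rank test only for overall survival.

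Calculation of sample size starts from "16 out of 94 (17%) STS patients treated with surgery and postoperative radiation therapy" and assumes an 80% relative reduction. It sets the error rates with "In a study design with an 80% risk of avoiding type II error, a 5% risk of type I error" and concludes "we will need to include 154 STS patients (77 in each group) in an RCT". Enrolment is then raised to 160 to allow for dropouts, of which few are expected. Study design describes a "non-blinded single-center randomized (1:1) controlled trial", and Randomization gives 80 patients per group. The sample-size section names neither a test nor a formula.

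**The concern.** The protocol fixes both the test and the power, so one can be checked against the other. Fisher's exact test is conservative when events are few. With about 17% and 3.4% of 77 patients, the expected counts are about 13 and 2.6 events, and the attainable p-values are coarse enough for the test to spend well under its nominal 5%. A sample size taken from the usual large-sample formula will then fall short of its target power.

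What is at stake is the accuracy of the stated type II error and the purpose of the extra six patients. If 154 evaluable patients do not give 80% power under the named test, those six are making up for the test and are not available to cover dropouts.

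**Working it through.** **Inputs.** Control rate 16/94 = 17.0%; 80% relative reduction, so NPWT rate 0.2 × 0.17 = 0.034; power 80%; type I error 5% (all from Calculation of sample size). Two-sided testing comes from Statistical analysis and 1:1 allocation from Study design.

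**Step 1: reproduce 77 per group.** Pooled normal approximation, no continuity correction:

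n = [1.960 × √(2p̄(1−p̄)) + 0.8416 × √(p₁(1−p₁) + p₂(1−p₂))]² / (p₁−p₂)²

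- p̄ = (0.17 + 0.034)/2 = 0.102, and p₁−p₂ = 0.136
- √(2 × 0.102 × 0.898) = √0.18319 = 0.4280; times 1.960 = 0.8389
- √(0.17 × 0.83 + 0.034 × 0.966) = √0.17394 = 0.4171; times 0.8416 = 0.3510
- n = (1.1899)² / 0.018496 = 76.55, rounded up to **77 per group, 154 in total**

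This is the protocol's figure. Of the other variants tried, none gives 77: unpooled variance gives 74, pooled variance in both terms 78, arcsine 69, continuity correction 91, and one-sided 61 (75 with correction). Using 16/94 unrounded also gives 77.

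**Step 2: exact power of the named test.** For n per group, sum Bin(i; n, 0.17) × Bin(j; n, 0.034) over all pairs (i, j) for which the two-sided Fisher p-value is below 0.05.

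| Evaluable per group | Total | Fisher power |
|---|---|---|
| 77 | 154 | 76.5% |
| 78 | 156 | 77.3% |
| 79 | 158 | 78.0% |
| 80 | 160 | 78.7% |
| 82 | 164 | 79.99% |
| 83 | 166 | 80.6% |

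The shortfall is 3.5 points at 154 and 1.3 points at 160. With 16/94 unrounded, the power is 76.6% at 77 and 78.7% at 80 per group. Doubling the one-sided Fisher p-value gives the same powers as the usual two-sided definition. One-sided Fisher at 5% would exceed 80% (84.7% at 77 per group), but the protocol specifies two-sided p-values. The continuity-corrected formula (91 per group) overstates what Fisher needs here.

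**Step 3: actual size and alternatives.** Size is the same sum with 17% in both arms.

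| Test | Power at 77 / 80 per group | Size at 77 / 80 per group |
|---|---|---|
| Fisher, two-sided | 76.5% / 78.7% | 3.0% / 3.1% |
| Boschloo | 80.5% / 82.4% | at most 5% at any common rate |
| Uncorrected chi-square, unstratified | 84.3% / 85.0% | 5.2% / 4.9% |

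Over common rates from 2% to 25%, the largest size of the uncorrected chi-square is about 5.3% at 77 per group and 5.2% at 80.

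**Step 4: sensitivity to the assumed effect.** With the control rate at 17%, Fisher power at 77 and 80 per group is 70.5% and 72.7% if the NPWT rate is 4%, and 80.3% and 82.4% if it is 3%.

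**The case against.** The strongest reply is that the gap is small. The trial plans 160 patients, expects few dropouts over 120 days, and is only 1.3 points short if all are evaluable; two or three more evaluable patients per group would close the gap. Step 4 shows that modest changes in the assumed NPWT rate move power by more than this. That stands, and it is why the point is minor. It does not remove the point, because the protocol attaches 80% to 154 patients and assigns the other six to dropouts.

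A second reply is that this is a condensed article, that the Fisher sentence is generic, and that an analysis plan not shown may specify the primary analysis further. Detail left to an analysis plan would be no finding. Here, however, the article states both a test and a power, and the two do not agree as written.

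A third reply is that the formula behind 77 is inferred. That is correct. The match is exact, but the protocol does not state its formula. The conclusion does not depend on it: whatever produced 77, two-sided Fisher at 77 or 80 per group does not reach 80%.

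A reader might infer more: that the primary analysis is invalid, that the trial is seriously underpowered on its own assumptions, or that the test must be replaced. The documents support none of these. Fisher's actual size of about 3% keeps the false-positive risk below the stated 5%, and nothing in the treatment comparison is biased. Nor is an uncorrected chi-square a cost-free replacement, since its size can slightly exceed 5%.

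**Conclusion.** The point holds as a minor one: the power statement is wrong as written. Under the only test named for a binary outcome, 154 evaluable patients give 76.5% power (a type II risk of 23.5%, not 20%) and 160 give 78.7%. Reaching 80% takes about 83 evaluable patients per group before any dropout allowance, so the choice of test absorbs the six-patient allowance and each dropout moves power back towards 76.5%.

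This rests on the protocol's own planning rates (17% and 3.4%), two-sided testing at 5%, equal groups, and reading the categorical-variables rule as covering the primary endpoint. The consequence is a modest loss of power under a valid, conservative test.

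**What to change.** Either of two changes is enough, and neither needs more patients or any change in conduct.

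1. Keep Fisher's test and correct the sample-size statement: for 17% versus 3.4% at two-sided 5%, power is 76.5% with 154 evaluable patients and 78.7% with 160. This costs one sentence.
2. Name Boschloo's exact test for the primary endpoint. It holds the 5% level and gives 80.5% and 82.4% at the existing sizes, so the six patients again serve as a dropout allowance. Because the trial is not blinded and recruitment has started, this needs a dated amendment, with its reason, made before any comparative analysis.

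If an uncorrected chi-square test or its stratified (Cochran-Mantel-Haenszel) form is preferred, the amendment should disclose that the unstratified test's actual size can reach about 5.3% at 77 per group. It should also say that the 84–85% power applies to the unstratified test; neither size nor power was computed here for the stratified version.

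### Randomisation is stratified by tumour location, but the only test named for the binary primary endpoint is a pooled Fisher's exact test, which ignores the strata and is too conservative to reach the stated 80% power

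*Protocol article*

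**What the plan says.** The Randomization section allocates patients 1:1 in blocks of 8, "stratified for upper extremity/truncal wall or lower extremity STS". The Discussion repeats the stratification and gives selection bias as the reason for it.

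The primary endpoint is binary: a major wound complication within 120 days of surgery. The only analysis sentence that covers it is "Fisher’s exact test will be used for categorical variables". No stratified or adjusted analysis is mentioned for any endpoint. The significance rule is "Two-sided *p*-values below 0.05 will be considered statistically significant".

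The sample-size section takes its control rate from an earlier trial in which the event "was identified in 16 out of 94 (17%) STS patients treated with surgery and postoperative radiation therapy", assumes an 80% relative reduction, sets 80% power and "a 5% risk of type I error", and concludes "we will need to include 154 STS patients (77 in each group) in an RCT". Enrolment is raised to 160 (80 per arm) to allow for dropout.

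**The concern.** The named test does not match two other parts of the design.

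1. **Randomisation.** Balance is forced on location, but a Fisher test on the pooled two-by-two table cannot use location. If location predicts wound complications, the pooled test overstates the null variance and becomes somewhat conservative.
2. **Sample size.** Fisher's test is conservative in its own right when events are few. If the 77 per arm came from a less conservative test, the planned analysis falls short of the stated power.

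The risk is a missed effect. Type I error is not inflated: both mismatches make the p-value too large rather than too small.

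**Working it through.** **Inputs from the article.** Control rate 16/94 = 17%; 80% reduction, so 0.17 × 0.2 = 3.4% with NPWT; two-sided alpha 0.05; power 80%; 77 per arm before dropout, 80 per arm enrolled.

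**Step 1: reproduce the stated size.** The pooled, uncorrected normal-approximation formula is

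n = [1.960·√(2·p̄·q̄) + 0.8416·√(p₁q₁ + p₂q₂)]² / (p₁ − p₂)²

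- p̄ = (0.17 + 0.034)/2 = 0.102, so √(2 × 0.102 × 0.898) = 0.4280
- √(0.1411 + 0.0328) = 0.4171
- n = (0.8389 + 0.3510)² / 0.136² = 1.4158 / 0.018496 = 76.5, rounded up to **77 per arm**

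This matches the article exactly. Other variants do not: unpooled variance gives 74, arcsine 69, continuity-corrected 91 and one-sided 61 per arm. The approximate power is 80.2% at 77 and 81.7% at 80 per arm.

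**Step 2: power of the test actually named.** This sums over every possible pair of event counts and rejects when Fisher's two-sided p is at most 0.05.

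| Per arm | Power, 17% v 3.4% | True type I error at a common 17% |
|---|---|---|
| 77 | 76.5% | 3.0% |
| 80 | 78.7% | 3.1% |

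Fisher first reaches 80% power at 83 per arm (166 in total, power 80.6%). Even full enrolment with no dropout falls short.

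**Step 3: add the strata.** The article gives neither stratum sizes nor stratum risks. The assumptions are: lower-extremity share 60% or 75%; control risk 1, 2 or 4 times as high in the lower extremity; overall control risk 17%; the same 80% reduction in both strata; equal allocation within strata. Results are from 200,000 simulated trials per scenario (60,000 for the exact stratified test).

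| Test | Power, 77 per arm | Power, 80 per arm | Null rejection, 80 per arm |
|---|---|---|---|
| Fisher, pooled | 76.5–77.0% | 78.6–79.2% | 2.7–3.1% |
| Exact stratified | 76.5–77.2% | 78.6–79.3% | 2.9–3.2% |
| Chi-square, pooled, uncorrected | 84.3–84.7% | 84.9–85.6% | 4.3–4.9% |
| CMH, uncorrected | 83.4–84.7% | 85.0–86.1% | 4.9–5.0% |
| CMH, continuity-corrected | 74.0–76.4% | 75.9–78.9% | 2.9% |

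A separate run of 20,000 trials at 80 per arm (70% lower extremity, control risks 21.5% and 6.5%) gave power of 79.1% for Fisher, 85.6% for pooled chi-square and 86.2% for uncorrected CMH, with null rejection of 3.0%, 4.6% and 5.0%.

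**Step 4: split the gain.** In that separate run, Fisher to pooled chi-square gains 85.6 − 79.1 = 6.5 points, and pooled chi-square to CMH gains 86.2 − 85.6 = 0.6 points. In the scenarios of Step 3 at 80 per arm, the second step is 0.1 to 0.5 points. At 77 per arm it ranges from −0.9 to +0.1. Between the two exact tests, the difference is −0.1 to +0.4 points.

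The strata add little because location can explain little of the variance. With a 60% share and risks of 24.3% and 6.1%, the between-stratum variance is 0.6 × 0.4 × (0.243 − 0.061)² = 0.0079. The total is 0.17 × 0.83 = 0.1411, so location accounts for about 5.6% of it, and this is the most favourable scenario considered.

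**Step 5: the point estimate.** With n_k patients per arm in stratum k, the Mantel-Haenszel weight is n_k·n_k/(2n_k) = n_k/2. The risk difference becomes Σn_k(p₁ₖ − p₀ₖ)/Σn_k, which is the crude difference. In the risk ratio the factors of one half cancel, leaving total NPWT events over total control events, which is the crude ratio. Blocks of 8 within strata keep the real trial close to equal allocation.

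**The case against.** **A reader might infer that ignoring the strata is what costs 6–7 points of power, or precision the design had already bought.** The figures do not support this: an unstratified chi-square recovers nearly all of the gain. Nor does the article support it. It justifies stratification by selection bias, its sample size takes no credit for stratification, and it gives no evidence on how strongly location predicts complications. If location is not prognostic, ignoring it costs nothing.

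**A reader might also infer that the pooled estimate answers a different question from the within-location comparison.** Under equal allocation within strata, the Mantel-Haenszel and crude estimates coincide, so this does not hold. The article also fixes no effect estimator to criticise.

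**Fisher is valid and defensible with few events.** This stands. About 80 × 0.17 + 80 × 0.034 = 16.3 events are expected. With a 75% share and a four-fold risk ratio, the upper extremity/trunk stratum (20 per arm) expects only about 20 × 0.052 = 1.0 control event. CMH is asymptotic, and its advantage vanishes if a continuity correction is applied. Its level was checked here only at an overall rate of 17%.

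**The article is condensed, and an analysis plan might add a stratified analysis.** That is possible, and the sentence on categorical variables is generic. But the article names a test rather than leaving the choice open, and that test does not fit its own sample size or randomisation.

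**Conclusion.** The point holds, at minor severity. The only test named for the primary endpoint ignores the randomisation strata. With about 79% power at 80 per arm and 76.5% at 77, it falls below the 80% on which the sample size rests. Its true type I error is about 3%, so part of the 5% allowance goes unused. These Fisher figures rest only on the article's own planning rates.

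The 85–86% for the stratified alternative at 80 per arm rests on the assumed stratum shares and risk ratios, but it varies little across them. The shortfall comes from Fisher's conservatism. Matching the analysis to the randomisation is good practice that costs nothing, but at this sample size it is worth only 0 to about 0.6 points of power at 80 per arm.

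**What to change.** State in the analysis section that the primary endpoint will be compared with a Cochran-Mantel-Haenszel test stratified by upper extremity/trunk wall versus lower extremity, **without continuity correction**, and reported as a Mantel-Haenszel risk difference or risk ratio with its 95% confidence interval. The same form suits the other binary wound endpoints. Add to the sample-size section which test the 77 per arm assumes, so that the two sections agree.

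The cost is a sentence or two. No extra patients are needed, and the stratum is already required for the randomisation in REDCap. Because recruitment has started, the change should be dated and made before outcomes are compared by arm. The trade-off is an asymptotic test in place of an exact one. If the team prefers to keep Fisher, it would need 166 evaluable patients at the article's own planning rates, more than the 160 planned.
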